## **9.3 QUALITATIVE STUDY ON ACCEPTABILITY AND PERCEPTIONS ON FEASIBILITY**

The qualitative study will involve health providers who are involved in the project and carers of children from the five arms. The aim of the study is twofold. The first aim is to understand to what degree health providers and care takers see IPTpd as a useful and welcome intervention that will improve children's health, and to what degree the intervention is seen as being worth the extra effort expected from health workers and carers (acceptability). The second aim of the study is to understand the feasibility of the different delivery mechanisms.

### 9.3.1 Health providers

Focus Group Discussions (FGDs) will be held with each of the following groups: i) health workers at hospital level, ii) village health workers, iii) health surveillance assistants (HSAs), and iv) District health management teams. For each group, two FGDs with different participants will be conducted in the beginning of the trial, and this will be repeated with the same participants (to the extent possible) when the trial is completed. The total number of FGDs will be 16. A central aim of the FGDs will be to assess the acceptability of IPTpd. In a setting where health providers often work under stress, how do they perceive the additional work burden that IPTpd represents? Do health providers expect additional remuneration, and does the lack of extra compensation have an effect on their motivation to implement IPTpd? To what degree do health providers believe that IPTpd is an important intervention to save children's lives, relative to other interventions? The FGDs will also aim to assess the adaptations that health providers need to make to their working practices in order to implement IPTpd, perceptions of the feasibility of implementing IPTpd through different delivery mechanisms, and recommendations on effective implementation. The information gathered through FGDs will be supplemented by ethnographic methodologies like observations and informal interviews. The FGDs will be conducted in the local language, Chichewa. All FGDs will be recorded, transcribed verbatim, translated to English and coded using software.

### 9.3.2 Carers of children:

A random selection of carers from the five arms will be conducted when the trial is completed. In each of the five arms, we will select four care takers of children who completed the treatment, and four who did not for in-depth interviews. The care taker will be the person who was with the child during hospitalization and who was recruited to the study. The total number of IDIs will be 40. The care takers will be interviewed at their homes and will be contacted by phone (own or neighbour's) for an appointment. Interview guides will be adapted to fit the issues pertinent to each of the groups (i.e. distance/transport and remembering the dates for OPD delivery, problems with access to working phones for SMS reminders, availability/presence of VHW/HSA etc). We believe that IDIs will be the best method for collecting sensitive and confidential personal information from care takers (including economic constraints, decision-making processes at household level and relationship with Village Health Workers/HSAs and providers at hospital level). In addition to IDIs, two FGDs in each arm will be conducted (one with those who completed the treatment and one with those who did not) to cover less sensitive and confidential themes and to get an idea of common norms. The total number of FGDs with care takers will be 10. Put together, the IDIs and FGDs will explore acceptability of IPTpd and perceptions of different models of delivery including facilitating and blocking factors. We will also map local/non-biomedical perceptions of anaemia which may have an effect on the utilisation of, and trust in, biomedicine. All IDIs and FGDs will be conducted in the local language and will be recorded, transcribed verbatim, translated, and coded using software.

## **10 Programme Management**

### **10.1 TRIAL AUTHORISATION**

Ethical clearance will be sought from the funding country, Norway as well as the Malawian regulator (the College of Medicine Research and Ethics Committee) and the Pharmacies and Poisons Board of Malawi.

### **10.2 TRIAL STEERING COMMITTEE**

Trial Steering Committee will provide independent oversight to ensure the trial progress; adherence to the protocol, patient safety and the integrity of the trial is protected. The TSC members will consist of trial PIs, trial statisticians and 3 independent members, including the independent chair. The TSC will meet every 6 months, virtually or face-to-face. The Data Safety Monitoring board will be appointed comprising of three independent internationally acclaimed experts in malaria and global health (one with statistical expertise).

### **10.3 TRIAL SPONSORSHIP AND QUALITY ASSURANCE**

The College of Medicine of the University of Malawi will be the trial sponsor for the delivery mechanism trial. Trial authorisation will be sought from Pharmacy, Medicines and Poisons Board). Clinical monitoring will be sub-contracted to an independent academic CRO; at least 3 visits are planned in the first year, including study initiation, and then 6-monthly thereafter until trial close out.

### **10.4 NATIONAL AND INTERNATIONAL COLLABORATION AND NETWORKING**

This project will be conducted in collaboration with various institutions. CIH-UIB recently received Centre of Excellence status for its Centre for Intervention Science in Mother and Child Health (CISMAC), with a 10 year 33m USD grant from the Research Council of Norway. The current proposal fits well with CISMAC's vision to 'undertake intervention research to support equitable improvement of maternal, neonatal and child health (MNCH) in low and middle income countries (LMICs) in sub-Saharan Africa'. If funded it may also compete for CISMAC collateral funding. Collaboration with Chr. Michelsens Institute (CMI) brings together the leading Norwegian institute in international health with the leading Norwegian institute in development studies. The project will establish a new, potentially strong South-South partnership between 3 research groups in Africa that are all national leaders in the area. The proposed grant will also enhance the North-South networking capacity by bringing together a number of well-established northern partners from Norway (1) CIH, (2) CMI; Europe (3) LSTM, (4) Imperial College London, UK (5) AMC, Univ of Amsterdam, the Netherlands; and USA (6) Univ of Minnesota. Together this partnership constitutes a new multi-centre trial network in endemic areas in Malawi, Uganda and western Kenya, capable of conducting large-scale definitive trials. Additionally the research sites in Malawi will be part of the Malawi-Zambia-Bergen NORHED proposal research platform that would support masters in epidemiology and research capacity building of the 3 institutions.

#### 10.4.1 Impact of the project and Key beneficiaries

This project is designed to generate the information required to assess whether IPTpd should be recommended as a cost-effective strategy for the post-discharge management of children with severe anaemia in malaria endemic areas. It is anticipated the trial results will increase the effectiveness of the management of severely ill children and reduce the health care costs associated with high readmission rates post-discharge, thereby also reducing associated costs to poor households. Women, who are the primary care takers and also key actors for households economic development, will be relieved and consequently improved welfare for households is expected. In the longer term, the ultimate beneficiaries of this research will be the children in sub-Saharan Africa, whose quality of life, health, welfare and creative output will be enhanced.

**WHO and other international stakeholders:** The beneficiaries include international organisations and funders of large scale malaria control initiatives such as the Global Fund, DFID, USAID and the US President's Malaria Initiative (PMI), and non-profit organizations such as the Malaria Consortium and MSF, which aim to improve malaria at regional and local levels and are instrumental in supporting countries to implement malaria control policies in sub-Saharan Africa.

**National policy makers and stakeholders:** Policy makers in Malawi will also benefit directly from the data generated by the trials: not only will they have the necessary country specific data on the safety, efficacy and cost effectiveness of PMC but also valuable information on effective delivery channels. Beneficiaries include the Ministry of Health, responsible for providing hospital services, and the National Malaria Control Programmes responsible for setting policy for malaria control with inputs from local research groups and leadership from WHO. Relevant departments of MOH in the countries are key collaborators in the trials and have been involved from the outset.

**Commercial private sector:** Sigma Tau, the manufacturer of Eurartesim (R) (the only Good Manufacturing Product [GMP] version of DHP and approved by the European Regular) and the 4 other manufacturers of generic formulations of DHP in China and Vietnam, will benefit from the data on the safety, efficacy and cost effectiveness for a new indication for the drug i.e. for chemoprophylaxis in young children recovering from severe anaemia.

#### 10.5 DIRECT ACCESS TO SOURCE DATA AND DOCUMENTS

The Investigator(s) will permit trial-related monitoring, audits, REC review, and regulatory inspections by providing the Sponsor(s), Regulators and REC direct access to source data and other documents (e.g. patients' case sheets, blood test reports, laboratory reports,).

### 11 Data Collection, Management and Analysis

The study will either use computer tablets or optical character recognition (OCR) software for creating and scanning (paper-based) data collection forms (Cardiff TeleForm). Completed CRFs and relevant source documents will be scanned on site and transferred daily (encrypted) to a central server at College of Medicine in Blantyre where they will be processed into databases via OCR. Data will be stored in MS Access and SPSS format. CrashPlan-Pro software will ensure automated encrypted back-ups to servers in cloud and at CoM via the internet.

### **11.1 DATA COLLECTION**

Data will be collected and recorded at the point of contact; i.e. either the health facility or at the participant's home by one of the trained study staff and VHV members. Site supervisors will check data collection forms at the end of each day for completeness and accuracy of recording. All uncompleted CRFs will be flagged and accordingly corrected using Good Clinical practices.

### **11.2 DATA ENTRY AND EDITING**

Data will be entered directly into tablets, Personal Digital Assistants (PDAs) or computer touch screens. These electronic data capturing gadgets will be pre-programmed and uploaded with electronic Case Record Forms (eCRFs) using Visual CE programming software. The eCRFs will have cross-checks for verification, validation rules and comply with Good Clinical Practices (GCP). These gadgets will be connected to a desktop allowing data to be directly uploaded into the database. The desktop will be installed with MS SQL server that automatically backs up data. The final data set will be transferred to statistical software programmes used for analyses, e.g, SAS, SPSS and other programmes.

### **11.3 DATA SHARING**

Anonymised data will be available to other researchers for further analysis, subject to ethical approval, the terms of the original participant consent and agreement on its use according to prevailing laws on intellectual property rights at partner institutes. The Partner institutions in the trial would automatically have the right to royalty free use of the data. For others, priority will be given to requests from Malawi. Access to aggregated data will be made readily available, whereas applications for individual participant datasets will be subject to a more stringent review process by the under the authority of the Project Management Committee (PMC) described earlier. The processes will be detailed and agreed in the institutional contracts to be signed by all partners. Information on data availability will be established by provision of an e-mail contact in publications and study reports, and on the project's web-page.

### **11.4 DATA STORING AND ARCHIVING**

Original data collection forms will be handled only by study staff and kept under locked storage until completely coded, checked and transported for data entry. Once data entry and cleaning are complete the original forms will be stored under lock and key at the TRUE until final analyses and reports have been prepared. The CRFs will be stored long term at the TRUE up to a minimum of 7 years. Data will be kept electronically at the TRUE and CoM in compliance with prevailing laws on data storage in all institutions. They will then be destroyed according to true policy and prevailing regulations in Malawi.

### **11.5 QUALITY ASSURANCE**

#### **11.5.1 Quality Control of the trial**

Monitoring of this trial will be conducted to ensure compliance with Good Clinical Practice and scientific integrity will be managed and oversight retained, by the sponsor. The Research Support Centre will be responsible for clinical monitoring of the trial on behalf of the sponsor.

GCP training will be provided to all staff/investigators by the Research Support Centre of the College of Medicine, the University of Malawi.

#### **11.5.2 Quality assurance/control of laboratory tests**

Regular audits of laboratory performance will be completed by experienced supervisors unconnected to the research study according to standard operating procedures. All malaria blood smears will be read by two different microscopists blinded to the RDT and each other's results, any significantly discordant results based on positive/negative result will be verified by a third expert microscopist. All RDTs will be stored and transported at the recommended temperatures and testing for malaria parasites will be done as per the instructions of the manufacturer.

#### **11.6 DATA HANDLING**

The Principal Investigator will act as custodian for the trial data. The following guidelines will be strictly adhered to:

Patient data will be anonymised

- All anonymised data will be stored on a password protected computer.
- All trial data will be stored and archived in Malawi in line with local regulations. Hard copies if any of CRFs will remain on site until completion of field work and stored long term at the Training and Research Unit of Excellence (TRUE)
- Electronic copies of the CRF and database will be archived with limited access.

#### **11.7 STATISTICS AND DATA ANALYSES**

##### **11.7.1 Sample Size and randomization**

Although a 2x2 factorial design will be used, only the main effects of "place of delivery" and "use of mobile phone reminders" are of primary interest. Each village cluster contributes 2 to 4 children/y with severe anaemia and there are 102 clusters in the catchment area. Assuming an intra-cluster correlation coefficient (ICC) of 0.1 and allowing for 20% loss-to-follow-up or efficiency loss due to varying cluster sizes, a sample size of 19 clusters of 5 children per arm (95 per arm, N=380 overall) has 80% power to detect a 25% absolute increase in coverage from an estimated 50% in the standard VHV or OPD groups to 75% in the arms supported by mobile phone reminders ( $\alpha=0.05$ ). The ICC of 0.1 is slightly more conservative than the ICC in a previous trial of delivery approaches for IPTc in the Gambia (0.08)[14].

The trial will use villages as the unit of randomisation; i.e. it is a cluster-randomised trial. This trial uses a factorial design and will evaluate two interventions, and will have 4 arms (factorial design). These kind of trials need to take the clustering in variation at village level into account, also called the design effect.

##### **11.7.2 Randomisation procedure**

The trial statistician [name] will computer-generate list of sets of matched clusters and forward these two to the PI. The allocation of clusters to either community-based or health facility-based intervention will occur at a public event prior to the trial. Village elders for 3 matched clusters will be asked to draw one opaque sealed envelope each from a box. Each envelope will contain the allocation. The allocation will be immediately recorded and sent to the study statistician, who in turn will provide the DSMB

statistician with a signed, dated copy in a sealed envelope with carbon paper inside to transfer hand written information onto the list inside the envelopes to create an audit trail.

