## 8 DESIGN AND METHODOLOGY

### 8.1 Trial Design

This is a single-centre, matched, cluster randomized, 5-arm, factorial design trial comparing the uptake of PMC-DHP delivered through health facility or community-based approaches with or without SMS/HSA reminders. All children will receive DHP and hence there are no placebo arms in this trial. However, children shall be randomized to receive PMC as follows:

- a. *Community-based*: Mother given **all** PMC drugs at discharge without an SMS reminder
- b. *Community-based*: Mother given **all** PMC drugs at discharge with an SMS reminder
- c. *Community-based*: Mother given **all** PMC drugs at discharge with HSA reminder
- d. *Facility-based*: Mother asked to return to outpatient departments (OPD) for each **monthly** PMC without an SMS reminder
- e. *Facility-based*: Mother asked to return to outpatient departments (OPD) for each **monthly** PMC with an SMS reminder

Where;

**Arm 1: Mother given at discharge without SMS reminder:** At discharge, the OPD staff will give the mother or guardian all drugs for PMC-1, PMC-2 and PMC-3 and instruct mother/guardian when to give these drugs.

**Arm 2: Mother given at discharge + SMS reminder:** At discharge, the OPD staff will give the mother or guardian all drugs for PMC-1, PMC-2 and PMC-3 and instruct mother/guardian when to give these drugs. Additionally they will be reminded via SMS to give the drugs to the child a date before each treatment course is due.

**Arm 3: Mother given at discharge + HSA reminder:** At discharge, the OPD staff will give the mother or guardian all drugs for PMC-1, PMC-2 and PMC-3 and instruct mother/guardian when to give these drugs. Additionally HSA or Village Health Volunteers (VHV) which are part of existing networks of community based volunteers taking part in village health committees will be reminded via SMS to go and remind the mother to give the drugs to the child a date before each treatment course is due.

**Arm 4: Mother given monthly at OPD without SMS reminder:** At discharge, the mother will be requested to return to the OPD to collect drugs for PMC-1, PMC-2 and PMC-3.

**Arm 5: Mother given monthly at OPD + SMS reminder:** At discharge, the mother will be requested to return to the OPD to collect drugs for PMC-1, PMC-2 and PMC-3. Additionally they will be reminded via SMS to come to the clinic to collect drugs a date before each treatment course is due.

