Alternative delivery strategies for PMC are to have the mother return to the health care facility to receive drugs for each treatment course. This is a plausible strategy as this occurs in many chronic illness cases where drugs are supposed to be collected from a health facility (e.g. in TB, HIV). In recent years there has been successful disease control programs operationalizing more decentralised drug delivery programs in the community. In this trial the mother may be reminded to come collect their child's PMC drugs using SMS ([Arm 4](#)) or not ([Arm 5](#)).

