#### 8.7.4 Enrolment

Once the parent/guardian provides informed consent for his/her child to participate in the study, the participant will be assigned a study ID and randomised to one of the five study arms.

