##### 8.7.4.2 Randomisation procedure at discharge

The unit of randomization will be the villages, defined as the smallest administrative unit overseen by a Village headman. A group Village headman oversees several villages. Ninety (90) villages in the catchment areas of Zomba district located in the southern region of Malawi will be involved in the study. Zomba Central Hospital participated in previous related studies [1, 15-17] and is particularly suitable for the delivery trial because of the existing linkages with community based health care providers and rural clinics within their catchment areas. A 1:1 allocation ratio will be used. To minimize imbalances across groups with respect to baseline malaria prevalence and risk factors for malaria, location-specific baseline information on malaria indicators, such as the prevalence of positive RDTs or microscopy in the 12-month period prior to the trial (Under-five registry data) will be considered in selection of villages.

Randomisation will be done by opening a single concealed envelope, which will contain the cluster and study arm.

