#### 8.12.4 1st, 2nd and 3rd PMC treatment schedules

The 1st, 2nd and 3rd PMC treatment will be given 2, 6 and 10 weeks following enrolment. These treatments will be given at home for those randomised to Arm 1, 2 or 3 and at OPD for those randomised to Arm 3 and 4 (Day 1 dose only, Day 2 and 3 will be at home). PMC uptake will be assessed by unannounced visits on day 4 or 5 after each treatment course by a research assistant. If children are found to be ill during these home-visits they will be referred to the study clinic for further evaluations as part of the unscheduled visits as described below.

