#### **11.7.4 Data Analysis**

The % of children receiving IPTpd according to schedule will be compared by relative risks (95% CI), adjusted for prognostic factors at baseline using log binomial or Poisson regression with adjustment for cluster effects. Hazard ratios will be calculated for morbidity endpoints using Cox regression for repeated events with robust standard error estimation methods to account for correlation between episodes within children. Incidence rates per child-year and absolute rate reductions will also be calculated.

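### Section 11.7.2 does not define an allocation to the five arms, conflicts with other sections on when and how villages are randomised, and the arm numbering is inconsistent

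*Protocol*

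**What the plan says.** **Design.** Protocol 8.1 states: "This is a single-centre, matched, cluster randomized, 5-arm, factorial design trial comparing the uptake of PMC-DHP". Three arms are community-based (no reminder, SMS, HSA) and two are facility-based (no SMS, SMS). Section 4.1 gives five arms at 1:1, and 8.7.4.2 repeats the 1:1 ratio.

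**The draw.** Section 11.7.2 says "The allocation of clusters to either community-based or health facility-based intervention will occur at a public event prior to the trial" and then "Village elders for 3 matched clusters will be asked to draw one opaque sealed envelope each from a box". It does not mention the reminder. Section 11.7.1, just before it, describes a 2x2 factorial with four arms.

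**Other accounts of randomisation.**
- 8.7.4: after consent, "the participant will be assigned a study ID and randomised to one of the five study arms".
- 8.7.4.2, whose title places the procedure at discharge: "Randomisation will be done by opening a single concealed envelope, which will contain the cluster and study arm". The same section names the village as the unit.
- 8.12.3.3: the arm depends on the child's cluster.
- 11.7.3: central block randomisation using baseline malaria risk, with villages as the unit.

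**Arm numbers.** In 8.1, Table 1 and Figure 1, number 4 is OPD without SMS and number 5 is OPD with SMS. Section 8.1.1 has these two the other way round. Section 8.12.4 puts Arms 1, 2 and 3 at home and then says "at OPD for those randomised to Arm 3 and 4".

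**The concern.** A randomisation section should let an independent statistician generate the allocation. This one does not. The set size (three) and the number of options (two) fit neither the five arms nor the 3:2 split between community and facility arms. The reminder comparison is specific objective 2 in 7.2 and a main effect of primary interest in 8.3, yet no randomisation step produces it.

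Timing matters too. The trial is open-label, the primary outcome is uptake, and 8.7.4.4 allows exclusion for suspected poor compliance with follow-up. If a village's arm is public before enrolment, that judgement can be made with the arm known. If the arm is revealed only after consent, it cannot. The reader cannot tell which protection applies.

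The arm numbers define the exposure being compared. Staff or programmers working from 8.1.1 or 8.12.4 would deliver or code something different from those working from Figure 1.

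**Working it through.** **Inputs.** Five arms at 1:1 (4.1, 8.1, 8.7.4.2). Sets of three and two options (11.7.2). Cluster counts: 90 villages taking part (8.2, 8.7.4.2), 102 clusters in the catchment (11.7.1), 125 clusters required (8.3). Children: 75 per arm, 375 in all (8.3).

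**1. The plan's cluster requirement.** For 50% against 75%, two-sided 5% (sidedness assumed), 80% power and unpooled variance:
- n = (1.960 + 0.842)² × (0.50×0.50 + 0.75×0.25) / 0.25² = 54.94 per arm.
- Design effect = 1 + ((1 + 0.036)×3 − 1)×0.1 = 1.2108.
- With 10% loss: 54.94 × 1.2108 / 0.9 = 73.9, so 25 clusters of 3 = 75 per arm and 125 clusters. The figure in 8.3 is reproduced, with 80.6% power at 75.

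**2. What the 11.7.2 draw gives with 90 villages (90/3 = 30 sets).** The target is 90/5 = 18 villages per arm, that is 54 community and 36 facility. Assume equal sub-allocation within each delivery mode; the protocol states none.
- A set of three splits 3:0, 2:1, 1:2 or 0:3, never 1:1 or 3:2.
- Independent 50:50 draws (assumed): 45/3 = 15 per community arm and 45/2 = 22.5 per facility arm on average.
- Two community envelopes and one facility envelope in every set: 60/3 = 20 and 30/2 = 15.
- One community and two facility in every set: 30/3 = 10 and 60/2 = 30.
- If every set splits 2:1 or 1:2, reaching 54:36 takes exactly 24 sets at 2:1 and 6 at 1:2 (48 + 6 = 54). No such rule is given.

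**3. If the box held the five arms instead.** With three of five arms drawn at random in each of 30 sets, simulation (10,000 draws) averages 18 villages per arm. The mean gap between the largest and smallest arm is about 7 villages, and all five arms reach exactly 18 in about 0.1% of draws.

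**4. Can sets of three be balanced?** Yes, by construction. There are 10 different triples of five arms, and each arm lies in 6 of them. Using each triple three times fills 30 sets and gives 6 × 3 = 18 villages per arm, with each pair of arms meeting in 9 sets. The protocol describes no such scheme.

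**5. Divisibility.** Sets of five: 90/5 = 18, 125/5 = 25, 102/5 = 20.4. Sets of three: 90/3 = 30, 102/3 = 34, 125/3 = 41.67.

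**6. Timing and mechanism.** A public draw before the trial (11.7.2), an envelope at discharge (8.7.4.2) and central block randomisation (11.7.3) are three different accounts of one step. They agree on the village as unit.

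**7. Arm key.** The reversal in 8.1.1 concerns Arms 4 and 5, which hold 2 × 75 = 150 of 375 children. Section 8.12.4 is inconsistent on Arms 3 and 5. Together three arms are touched (3 × 75 = 225 children). These are children in arms with conflicting labels, not children shown to be misallocated.

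**The case against.** Three stronger readings are tempting, and the documents do not support them.

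*Sets of three make five balanced arms impossible.* A reader might infer this because no set of three can hold all five arms. Step 4 shows that overall balance is still attainable. The fault is that the text defines no scheme that attains it.

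*The trial switches to randomising children, so one village could fall in several arms.* That needs the enrolment sentence in 8.7.4 to be read alone. Sections 8.7.4.2, 11.7.1 and 11.7.3 name the village as the unit, the envelope in 8.7.4.2 holds the cluster as well as the arm, and 8.12.3.3 ties the arm to the cluster. The conflict is over timing, mechanism and concealment.

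*The analysis ignores the matching.* Section 11.7.4 adjusts for baseline prognostic factors and specifies models "using log binomial or Poisson regression with adjustment for cluster effects". It is silent on matched sets and does not exclude them. Their handling may properly sit in a statistical analysis plan, which is not at hand. The protocol also gives no figure from which the precision gained by matching could be sized.

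It can also be said that the arm numbers are slips in narrative text, since 8.1, Table 1 and Figure 1 agree. That stands as a reason to treat the labels as an editorial correction, but they still have to be corrected. None of these replies supplies a five-arm draw or a step that allocates the reminder.

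**Conclusion.** The point holds as a defect of specification. Section 11.7.2 does not define an allocation to the five arms and never allocates the reminder; 11.7.1 describes a different, four-arm design; and 8.7.4, 8.7.4.2 and 11.7.3 contradict 11.7.2 on timing and mechanism. This needs correcting because every between-arm comparison rests on it.

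The possible imbalance depends on how the gap is filled: about 15 against 22.5 villages per arm under an even two-option draw, 20 against 15 or 10 against 30 with fixed envelopes, and none under a deliberately balanced scheme. These figures assume 90 villages and equal sub-allocation. The arm-key conflicts touch three of five arms and are a smaller, editorial matter.

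**What to change.** - **11.7.2:** form matched sets of five villages on the prior-year malaria indicators already named in 8.7.4.2, with each set drawing Arms 1 to 5 once before enrolment. Alternatively, keep sets of three and write out a balanced incomplete-block scheme such as that in step 4.
- **Number of sets:** settle the cluster count first. 90 villages give 18 sets of five, 125 give 25, and 102 does not divide by five (20 sets use 100 and leave 2). This choice affects power. With 18 villages per arm and 3 children each, effective n is 54×0.9/1.2108 = 40.1 and power about 67%. With 75 children per arm from 18 villages (mean 4.17, same variation in cluster size assumed), the design effect is 1.332, effective n is 67.5/1.332 = 50.7 and power about 77%. Both are unpooled, against 80% in 8.3.
- **8.7.4 and 8.7.4.2:** state that each child takes the arm of the village, and what, if anything, an envelope at discharge is for.
- **11.7.1 and 11.7.3:** align with the five-arm draw.
- **Arm key:** reconcile 8.1.1 and 8.12.4 with 8.1, Table 1 and Figure 1, and use one key throughout.
- **If villages are already allocated** (4.1 lists the trial as recruiting): document the procedure actually used, the actual sets and the resulting villages per arm. Do not redraw on paper.

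Before allocation the cost is protocol wording and the decision on cluster count. A matched-set term in the model is at most a suggestion for the statistical analysis plan.
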